### Outcomes

#### Primary Outcome

A summary of pre-planned study outcomes is shown in Textbox 1. The primary clinical outcome of this study is BP change from baseline. This outcome will be assessed as a continuous variable (separately for both diastolic and systolic BP change from baseline) and dichotomous variable (sustained control, defined as BP <140/90 in 2 or more consecutive visits during the trial). As this study was initiated before the 2017 BP guidelines, <140/90 was used to define control; this value also aligns with current KDIGO recommendations [17,46]. Rates of control at the end of the intervention period and 6 months later will be assessed based on the most recent BP measurement carried forward.

Outcome measures. ACEi/ARB: angiotensin converting enzyme inhibitor / angiotensin II receptor blocker; BPA: best practice advisory; CKD: chronic kidney disease; PCP: primary care provider; NSAID: nonsteroidal anti-inflammatory drug.**Primary outcome:** blood pressureSystolic blood pressure changeDiastolic blood pressure changeControlled blood pressure (defined as <140/90)

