## Methods

### Overall Design

This was a 3-arm cluster randomized controlled trial with randomization at the provider level. There was 1 usual care control arm and 2 intervention arms. For patients of PCPs in the intervention arms, the research team ordered triple-marker testing (serum creatinine, serum cystatin-c, and urine ACR) at the beginning of the study period, to be completed when the patient visited the lab for regular clinical care. The eCDSS launched for PCPs and patients in the intervention arms during a regular PCP visit subsequent to completing the triple-marker testing. Patients in the eCDSS+ arm also received a pharmacist phone call to reinforce CKD-related education after a PCP visit in which the eCDSS was utilized. We planned for an 18-month trial beginning October 4, 2017, that included a 12-month intervention period and subsequent 6-month follow-up period. This trial was registered on ClinicalTrials.gov (NCT02925962). The University of California San Francisco Human Research Protection Program approved the protocol for this study.

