### Eligibility and Selection of Participants

All providers practicing at the general internal medicine practice with a primary care panel were eligible for inclusion and randomization.

Eligible patients were identified using a previously described and validated algorithm [40]. (Patients were considered eligible for inclusion if they were aged 18 to 80 years; had a preferred language of English, Spanish, or Chinese; had at least 2 outpatient eGFR_Cr_=30 to 59 milliliters/minute (mL/min) at least 90 days apart, one of which was within the 12 months before August 14, 2017 (when providers were first contacted for study recruitment); and had a primary care visit in the past 18 months. (see Figure 1 for the Consolidated Standards of Reporting Trial diagram) Participants were automatically excluded (based on EHR data) if they were deceased; diagnosed with end-stage renal disease; engaged with a nephrology clinic with 2 or more visits in the past 12 months; kidney transplant recipients; or diagnosed with dementia. PCPs were then sent a list of potential participants for inclusion and asked to exclude participants for additional criteria that were unreliably captured when extracted from the EHR: current pregnancy, life expectancy <6 months, limited communication ability owing to impaired cognition or severe mental illness, New York Heart Association Class III/IV heart failure, or known ejection fraction <25%. PCPs could also exclude any other participants they felt would be inappropriate for study staff to contact.

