### Intervention

Before the eCDSS rollout but after randomization, all participating PCPs randomized to an intervention arm were asked to watch an educational video that provided background on guideline-based CKD care, as well as information on what to expect when an enrolled patient participant came in for a visit. PCPs were given an incentive of US $10 and a chocolate bar upon watching the video. Overall, 69.8% (72.0% eCDSS and 67.9% eCDSS+) viewed the video.

Before the eCDSS rollout, between October 5, 2017 and October 12, 2017, one of the study investigators (LK) ordered triple-marker testing for each patient participant from the eCDSS arm (n=169) and each patient participant from the eCDSS+ arm (n=177). We excluded 48 patients who opted out. In total, 10 patients withdrew later.

After the triple-marker testing was ordered, the next time the patient participant visited the lab for their regular clinical care, the triple-marker labs were also collected. We programmed the eCDSS to trigger the first time that the patient participant visited their PCP after all 3 lab results were available. (see Figure 2 for the study workflow) The eCDSS best practice advisory (BPA) appeared above the current medications in the electronic chart (Figures 3 and 4). PCPs could choose to open the BPA by clicking an “accept” button. We also allowed PCPs to view the recommendations by hovering over the BPA before accepting it. For patient participants categorized as low risk, when the PCP accepted the BPA, triple-marker labs with an expected completion date 6 months hence prepopulated were automatically pending for the PCP to sign. For patient participants categorized as high risk, when the PCP accepted the BPA, a SmartSet (EpicCare, Epic Systems) of tailored orders and recommendations appeared (Figure 5). If the PCP did not open the BPA and sign the orders in the SmartSet during the first PCP visit after the triple-marker labs were available, the BPA would trigger at up to 2 additional PCP visits during the study period. The eCDSS did not trigger if the patient participant saw a provider who was not their PCP.

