### Data Collection

For patient participants, the EHR was used to collect baseline data about demographic characteristics (age, sex, race-ethnicity, preferred language, and insurance status); medical co-morbidities (cerebrovascular disease, congestive heart failure, coronary artery disease, diabetes mellitus, hyperlipidemia, and hypertension); current medication prescriptions (statin, ACEi/ARB, and diuretics); previous documentation of CKD on problem list and/or as a visit diagnosis, most recent blood pressure, eGFR­­_Cr,_ eGFR­­_Cys_ (if available), and urine ACR (if available) before enrollment.

Primary outcome data on BP will be extracted from the EHR. Baseline BP was defined as the most recent ambulatory BP measurement before final enrollment on October 4, 2017. All patient participant ambulatory BP measurements were collected during the intervention period and will continue to be collected for the 6 months after the end of the intervention.

Secondary outcomes will be collected primarily using automated EHR data extraction algorithms. The outcomes acquired through data extraction include all secondary outcomes except for provider and patient-centered outcomes, which are collected via surveys. Up to 25 participants in each of the 3 arms were surveyed to assess patient knowledge about CKD and NSAID avoidance. Patient participants in the eCDSS arm were surveyed 2 weeks after a visit in which the SmartSet was utilized; those in the eCDSS+ arm were surveyed 2 weeks after their pharmacist follow-up call, and those in the usual care arm were surveyed 2 weeks after a visit with their PCP during the study period. All participating intervention PCPs will be surveyed about their perception of the feasibility and utility of the eCDSS and pharmacist calls (for CDSS+ providers).

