#### Completion of Triple Marker

Of the 336 patient participants in the intervention arms, 178 (53.0%) completed the triple-marker screening.

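### BP control at months 12 and 18 rests on the last reading carried forward, with no window and no required post-baseline reading, so stale values can count as outcomes

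*Protocol article*

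**What the plan says.** The Primary Outcome section names systolic change, diastolic change and BP control (<140/90). For control at the end of the intervention and six months later, it says the rates "will be assessed based on the most recent BP measurement carried forward". The Overall Design section places these time points at months 12 and 18: the trial "included a 12-month intervention period and subsequent 6-month follow-up period".

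The Data Collection section defines the starting value: "Baseline BP was defined as the most recent ambulatory BP measurement before final enrollment on October 4, 2017". It also says what is held: "All patient participant ambulatory BP measurements were collected during the intervention period and will continue to be collected for the 6 months after". The source is the health record, and no study BP visit is described. Under Eligibility, the only stated requirement on primary care contact is that the patient "had a primary care visit in the past 18 months".

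Exposure starts at a different date for each patient. The Intervention section says the tool was programmed to "trigger the first time that the patient participant visited their PCP after all 3 lab results were available".

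The Analyses section plans an intention-to-treat analysis by GEE. It adds an inverse-probability-weighted sensitivity analysis for differences by arm in the number of assessments or visits.

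**The concern.** A carry-forward rule needs an earliest admissible date, and none is stated. Followed as written, the rule allows three things:

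- A patient with no reading after 4 October 2017 can keep the baseline reading as both the month-12 and the month-18 outcome.
- A patient whose last reading was taken before or at the visit where the tool fired contributes a value that cannot reflect orders signed at that visit.
- A patient with no reading between months 12 and 18 has the same value at both time points, so the later result partly copies the earlier one.

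The first two can pull the arms together. If the share of stale values differs by arm, the contrast can also be biased in either direction. The Limitations section already concedes reduced power for the primary outcome.

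**Working it through.** **The plan's own figure.** The only power figure is for BP change. With 23 clusters of 15 per arm, ICC 0.025 and SD 5 mmHg:

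- Design effect = 1 + 14 × 0.025 = 1.35.
- SE = 5 × √(2 × 1.35/345) = 0.442.
- With t on 44 degrees of freedom, the detectable difference is 1.27 mmHg, as stated.

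That calculation is not in dispute. The article gives no figure for control rates.

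**Can stale readings occur?** Setting the sections side by side:

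- Eligibility asks for one primary care visit in 18 months, so gaps in primary care longer than the 6-month follow-up, or the 12-month intervention, are admitted.
- "Of the 336 patient participants in the intervention arms, 178 (53.0%) completed the triple-marker screening". Of these 178, 138 had a later PCP visit in the intervention period, so 40/178 = 22.5% did not. These are counts of PCP visits, not of missing BP. They show sparse contact and do not measure stale readings.
- Follow-up in the pharmacist arm is by telephone, so it does not itself produce a clinic reading.

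**What dilution would mean (illustration only).** Let f be the share in each arm whose control status is a carried baseline value. Those patients show no arm difference beyond any baseline imbalance. If they would otherwise have shown the average effect, the observed difference is D × (1 − f), and the sample size needed grows by 1/(1 − f)².

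Inputs from the article:

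- 524 patients and 79 PCPs over three arms, so on average 524/3 = 174.7 patients and 26.3 PCPs per arm, or 6.63 patients per PCP.
- ICC 0.025, applied here to control by assumption. Design effect = 1 + 5.63 × 0.025 = 1.141. Effective n = 174.7/1.141 = 153.1 per arm.
- Comparator control rate p₀ = 373/524 = 71.2% (the baseline table).

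Assumed inputs: a true difference D of 10 points, and f from 0 to 30%.

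Power = Φ{[Δ − 1.96√(2p̄(1−p̄)/n)] / √([p₀(1−p₀)+p₁(1−p₁)]/n)}, with n = 153.1, Δ = D(1 − f), p₁ = p₀ + Δ and p̄ the mean of p₀ and p₁. At f = 0 this is Φ[(0.100 − 0.0954)/0.0484] = 54%.

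| f | Observed difference | Power | Sample-size factor |
|---|---|---|---|
| 0 | 10.0 points | 54% | 1.00 |
| 5% | 9.5 | 49% | 1.11 |
| 10% | 9.0 | 45% | 1.23 |
| 20% | 8.0 | 37% | 1.56 |
| 30% | 7.0 | 29% | 2.04 |

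**Unequal staleness.** If control changes by d in both arms alike and the carried shares differ, a spurious difference of d × (f_usual − f_intervention) appears. With d = 5 points and a 10-point gap in f, this is 0.05 × 0.10 = 0.5 points. With d = 10 points and a 20-point gap, it is 0.10 × 0.20 = 2 points. Both inputs are assumed.

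**The case against.** The strongest reply has five parts.

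1. **Scope.** The rule is stated only for control rates at two time points. A reader might infer that continuous BP change is also carried forward, because the article gives no other derivation. That does not follow: a condensed article may leave the derivation to its analysis plan. Sustained control has its own rule, based on consecutive visits. This limit stands in full.

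2. **Baseline is not expressly carried.** The article defines baseline separately from the readings collected later, and a window could sit in an analysis plan not shown. So a baseline reading can become the outcome; the text does not say that it does. But carry-forward itself is stated, and nothing shown restricts it.

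3. **Age of the baseline reading.** A reader might take the 18-month visit criterion as the age of the baseline BP. It is an eligibility criterion on primary care visits. Patients also needed an outpatient eGFR within the 12 months before 14 August 2017, and any ambulatory reading counts. The age of the baseline BP is not documented.

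4. **The weighted sensitivity analysis.** It is aimed at differing visit counts by arm, and so at part of the bias. It leaves carry-forward in place for the main control rates and limits no reading's age.

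5. **Exposure.** A reader might combine dilution from carry-forward with the 102/336 intervention patients for whom the advisory was opened. That risks double counting. Those 102 had a PCP visit during the trial, so patients with only a baseline reading are likely to be found mainly among the unexposed, whose small effect already counts under intention-to-treat. Timely readings from unexposed patients are legitimate outcomes, and the training video came before the tool. A reading from month 11 carried to month 18 may also still hold some treatment effect. For these reasons 1 − f is a simplification that may overstate the loss.

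**Conclusion.** The point holds for the two control-rate time points. The stated rule allows baseline and pre-exposure readings to count as outcomes, and lets month 18 repeat month 12. It is a choice already made in the text, and the planned sensitivity analysis does not undo it.

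The direction is dilution when stale shares are similar across arms, with possible bias when they differ. The size is unknown, because the article reports neither visit frequency nor the number of patients without later readings. The power figures above rest on an assumed f, an assumed 10-point difference, and an effect spread evenly over patients. They show how sensitive the result could be and do not estimate a loss. The documents support no fixed percentage loss and no conclusion about continuous BP change. The change is worth making because the needed data are already collected.

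**What to change.** For control at months 12 and 18 only:

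- Count only post-baseline readings within a stated window before month 12 for the first time point, and within months 12 to 18 for the second.
- Estimate the arm contrasts with a logistic repeated-measures model on those readings, adjusted for baseline BP. Use either patient and PCP random effects, or the planned GEE with inverse-probability weights for visit frequency.
- Report by arm how many patients have no reading in each window.
- Keep last-value-carried-forward as a sensitivity analysis, stating whether baseline may be carried.

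The cost is some extra programming and no new data. The downside is an added assumption. The random-effects model needs missing-at-random. Weighted GEE needs a correct model for visit frequency, and unweighted GEE would not give that protection. Routine-care readings may also be informative in timing, because patients with uncontrolled BP may be seen more often; the model or weights should allow for this.

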**Secondary outcomes**
ProcessPCP awareness of CKD diagnosis (CKD inclusion on problem list or visit diagnosis)ACEi/ARB utilization for albuminuriaStatin therapy for eligible high-risk CKD patientsInitiation of statin therapyTotal use of statin therapyPatient-centeredKnowledge about CKDAwareness of NSAID avoidance in CKD
**Implementation outcomes**
ReachRecruitment rate of providers and patientsProportion that complete triple marker screenProportion with PCP visit after complete triple marker screeningProportion of participants where BPA is available for PCPProportion of participants identified as high- vs low-risk CKDAdoptionProportion where PCP signed Smart Set when BPA was availableProportion of CDSS+ participants that received pharmacist phone call after PCP signed Smart SetImplementationProportion of orders signed or patient education provided by PCP after opening Smart SetProportion referred to nephrology and followed up with nephrology after signing Smart SetProportion of low-risk CKD patients that receive repeat triple screenMaintenancePCP satisfaction with eCDSSPCP intent to continue using eCDSS

#### Secondary Outcomes

Our main secondary outcome is PCP awareness of the patient participant’s CKD diagnosis, as measured by inclusion of CKD-related International Statistical Classification of Diseases and Related Health Problems-10th Revision codes on the problem list or as a visit diagnosis. Additional secondary outcomes include process of care, patient-centered, and implementation outcomes.

There are 2 main process of care outcomes: (1) the proportion of patient participants with albuminuria prescribed ACEi/ARB and (2) appropriate use of statins. Appropriate statin use is defined both as the proportion of all patient participants aged ≥50 years prescribed statin therapy and the proportion of participants initiated on statin therapy after study start date.

Patient-centered outcomes include patient knowledge about CKD and NSAID avoidance as measured by patient surveys.

In addition to the effectiveness outcomes described above, the implementation outcomes are described in detail in Textbox 1 using the reach, effectiveness, adoption, implementation, and maintenance (or RE-AIM) framework to highlight measures crucial to successful implementation [47]. In this paper, we report initial implementation results, including all of the Reach outcomes and the first Adoption outcome (PCP SmartSet use).

### Analyses

Baseline demographic and clinical characteristics will be summarized and study balance by study arm will be assessed using descriptive statistics as well as methods that account for the lack of independence among patients in the same cluster [48]. Balance will be assessed with logit link generalized estimating equation (GEE) for categorical variables and linear GEE models for continuous variables. Clustering will be accounted for using an exchangeable correlation matrix with robust standard errors. We anticipate controlling for characteristics that are associated with outcomes but differ at baseline between arms and using multivariable regression analyses with GEE to account for cluster randomization in the reporting of the final outcomes of our study. Sensitivity analyses will include *as treated* analyses with inverse probability weighting to determine impact of participants changing providers/study arms as well as to determine impact of any differences in the number of assessments or clinic visits by study arm. Primary analyses will follow intention-to-treat principles.

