### Randomization and Blinding

We utilized block randomization at the PCP level based on panel size. The study statistician randomized PCP participants to each of the 3 study arms using an automated procedure that accounted for cluster size, to assure balance both in terms of number of patients and number of providers per arm. Eligible patient participants were assigned to study arms based on their PCP’s assignment. The study statistician was blinded to the identification of the PCPs and patients and will be similarly blinded for the analyses.

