### Sample Size and Power Calculation

Based on preliminary data from our institution’s EHR, it was determined that there would be a maximum of 1400 participants in the practice who could meet inclusion criteria. The study was powered for the clinical outcome of BP change, with calculations performed using the clustersampsi command for Stata version 11.2. We assumed a 2-tailed alpha level of 0.05, an intraclass correlation coefficient of 0.025 based on studies in primary care settings [49,50], and a standard deviation of 5 mmHg. Assuming 23 clinicians per arm with at least 15 patients per clinician (ie, 345 patients per arm), we estimated that we would have 80% power to detect a difference as small as 1.27 mmHg between arms.

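### Covariate adjustment hinges on observed baseline imbalance, so baseline BP may stay out of the BP-change models and precision is lost

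*Protocol article*

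**What the plan says.** In the protocol article, Primary Outcome states: "The primary clinical outcome of this study is BP change from baseline". The continuous form is analysed "separately for both diastolic and systolic BP change from baseline", alongside a dichotomous control outcome.

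The Analyses section plans multivariable GEE regression for the final outcomes and gives one criterion for the covariates: "We anticipate controlling for characteristics that are associated with outcomes but differ at baseline between arms". Whether arms differ is judged on the trial's own baseline data: "Balance will be assessed with logit link generalized estimating equation (GEE) for categorical variables and linear GEE models for continuous variables". Descriptive statistics are also to be used, and no threshold for a difference is given. No covariate is named as fixed.

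Baseline BP is available. Data Collection says: "Baseline BP was defined as the most recent ambulatory BP measurement before final enrollment on October 4, 2017". Panel size was part of the allocation. Randomization and Blinding says: "We utilized block randomization at the PCP level based on panel size". Neither variable is committed to an outcome model.

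**The concern.** The rule has two conditions, association with the outcome and a difference between arms, and a covariate must meet both. Precision depends on the first alone. A variable that explains much of the outcome reduces the residual variance whether or not the arms happen to differ on it. Under randomisation most such variables will look balanced, so the rule tends to discard the ones that would help most.

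For the BP-change models, baseline BP would therefore enter only after a chance imbalance. Otherwise the comparison rests on a raw change score, which uses baseline by subtraction with the coefficient fixed at 1. Regression estimates that coefficient, and so is more precise. It also deals with regression to the mean after a chance baseline difference, which subtraction does not.

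The trial has little precision to spare. It was planned at 345 patients per arm and enrolled 188, 165 and 171. The Limitations section acknowledges that power for the primary outcome is affected.

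**Working it through.** **1. The plan's own figure.** Inputs from Sample Size and Power Calculation: SD 5 mmHg, ICC 0.025, 23 clinicians per arm, 15 patients each, two-sided alpha 0.05, power 80%.

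- Design effect: 1 + (15 − 1) × 0.025 = 1.35.
- SE of the difference: 5 × √(2 × 1.35/345) = 0.442.
- Detectable difference: (t₀.₉₇₅ + t₀.₈₀ on 44 df) × SE = 2.865 × 0.442 = 1.267, which reproduces the stated 1.27 mmHg.

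The calculation contains no covariate term.

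**2. Change score against regression adjustment.** Let s be the SD of BP at each time and r the baseline-to-follow-up correlation.

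- Variance of the change score: 2(1 − r)s².
- Residual variance after adjustment for baseline: (1 − r²)s².
- Ratio: (1 + r)/2, which is below 1 for every r < 1.

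The article does not give r, so a range is assumed. Here the plan's 5 mmHg is read as the SD of the change score, and the planned size is kept.

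| r (assumed) | Variance ratio | SE reduction | Detectable difference, from 1.27 mmHg | Power at 1.27 mmHg, from 80% |
|---|---|---|---|---|
| 0.3 | 0.65 | 19% | 1.02 | 94% |
| 0.5 | 0.75 | 13% | 1.10 | 90% |
| 0.7 | 0.85 | 8% | 1.17 | 86% |
| 0.8 | 0.90 | 5% | 1.20 | 84% |

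**3. Enrolled numbers and the observed BP spread.** Table 1 gives a median baseline systolic BP of 128 with quartiles 117 and 140. The normal-equivalent SD is (140 − 117)/1.349 = 17.05 mmHg. At r = 0.5 the change-score SD equals s, because 2(1 − 0.5) = 1. Mean cluster size is 524/79 = 6.63, so the design effect is 1 + 5.63 × 0.025 = 1.141, ignoring unequal cluster sizes.

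- Usual care against eCDSS (188 and 165): SE = 17.05 × √(1.141 × (1/188 + 1/165)) = 1.943. Detectable difference 2.857 × 1.943 = 5.55 mmHg unadjusted, and 5.55 × √0.75 = 4.81 adjusted.
- Usual care against eCDSS+ (188 and 171): 5.50 unadjusted, 4.76 adjusted.

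The result depends on r. For the first pair, r = 0.3 gives 5.55 × √1.4 = 6.57 falling to 5.55 × √0.91 = 5.29. At r = 0.8 it is 5.55 × √0.4 = 3.51 falling to 5.55 × √0.36 = 3.33.

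**4. How much the stated rule recovers.** A two-arm simulation used 26 clusters of 7 per arm, ICC 0.025, SD 17 and 4,000 runs. The rule was represented by an assumed 5% test of baseline BP. That test brought baseline BP into the model in about 5% of trials.

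| r | Power for 5 mmHg: change score | Imbalance rule | Always adjusted |
|---|---|---|---|
| 0.4 | 64% | 65% | 79% |
| 0.5 | 74% | 75% | 84% |
| 0.6 | 83% | 83% | 89% |
| 0.7 | 92% | 93% | 96% |

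Under the null, the imbalance rule rejected in 3.9% to 4.6% of trials.

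**The case against.** **The wording is soft.** The sentence says what the authors anticipate. It does not exclude other covariates and sets no threshold, and an analysis plan that fixed baseline BP would not contradict it. That is fair, and it means the 5% screening test in the simulation is an assumption. But imbalance is the only criterion the article gives, so this is a stated rule and not a silence left for the analysis plan to fill.

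**Baseline BP is already used.** The change score subtracts it, so it would be too strong to say that the main predictor is ignored. This stands. The loss is the difference between a change score and regression adjustment, and that is all the figures above measure.

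**The size rests on unsourced inputs.** The correlation is not in the article, and the 17 mmHg SD comes from baseline quartiles and is not the plan's 5 mmHg. This also stands. The direction holds for every r < 1; the amount does not come from the documents.

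**Stronger readings that the documents do not support.** A reader might infer that data-driven selection gives p-values the wrong reference distribution and inflates type I error. The simulation above shows no inflation. A second one, with unequal clusters and uncorrected robust standard errors at r = 0.5, rejected 5.8% to 6.1% with selection and about 6.5% without.

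A reader might also infer that confidence intervals will be too narrow for want of a small-sample correction. The article says "Clustering will be accounted for using an exchangeable correlation matrix with robust standard errors" and is silent on corrections. That sentence follows directly on the balance models, and the choice of sandwich estimator is ordinary analysis-plan detail, so it is no part of this point.

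**Blanket adjustment would not work.** The patient survey outcomes are collected only after a visit or call, so they have no baseline value. Baseline statin use does not vary among patients who can still initiate a statin. The number and size of the randomisation blocks are not reported, so a full set of block effects could use many degrees of freedom. These limits shape the fix.

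**Conclusion.** The point holds as one of efficiency. Choosing covariates by observed imbalance would usually leave baseline BP out of the BP-change models, and adjusting for it always is more precise for any r < 1. The standard error would be about 5% to 19% smaller for r from 0.8 to 0.3. At r = 0.5 that takes 1.27 to about 1.10 mmHg on the plan's SD and size, or about 5.5 to 4.8 mmHg for systolic BP on the enrolled numbers with an SD near 17 mmHg. These figures assume r, equal BP variance at both times and an unchanged ICC.

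The variance formula covers only the continuous BP outcomes; no gain is quantified for the binary ones. The gain from a panel-size term cannot be calculated from the article and is probably small. Its case is that the analysis should reflect the randomisation. The validity of the tests is not in question here.

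**What to change.** In Analyses, replace the imbalance-based rule with a prespecified model, fitted whatever the observed balance, that contains:

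- study arm;
- the baseline value of the outcome: baseline systolic or diastolic BP for the matching BP-change model, baseline control status or BP for the control outcome, and baseline status for other outcomes where one exists and varies;
- panel size as a simple covariate, for example a single term.

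Use the balance tables descriptively, and keep adjustment for observed imbalances as a sensitivity analysis.

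The cost is a sentence or two of text and one or two degrees of freedom. Baseline BP is already extracted and panel size was used at randomisation, so no new data are needed. The article still describes the final outcome analyses as future work, so the change can precede them. For binary outcomes under a logit link, adjustment makes the odds ratio conditional on the covariates, so the plan should say which effect measure it reports.
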